By using an initially liquid biomaterial, which polymerizes after being injected, the cells adhere much better to the disc tissue. NOVOCART™ Disc plus (NDplus), an autologous cell compound for autologous disc chondrocyte transplantation (ADCT), was developed to provide rehydration and maintain the biological integrity of degenerative lumbar discs to prevent secondary diseases such as recurrent lumbar disc herniation, osteochondrosis, or segmental instability. The important properties of NDplus are anti-inflammatory, antiangiogenic and antiosteogenic. Moreover, NDplus is hydrophilic, supports cell morphology, and stabilizes the chrondrogenic phenotype.

In this phase-I/II study, NDplus is being investigated for its clinical applicability, safety, and efficacy in the repair of herniated, nucleotomized discs and of adjacent degenerated discs, if present.

The objective of this clinical study is to provide the basis for a confirmatory study design (endpoints and methodologies) (phase II) and to develop a safety profile for the surgical procedure as well as for NDplus (phase I). This study further aims at developing and validating known and new biologic markers for the quality and clinical efficacy of NDisc plus as requested in the context of identity, purity, and potency characteristics of the medicinal/investigational product.

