Secondary outcome parameter	Changes in health status and quality of life will be captured by the Short Form-36 (SF-36) version 2.0 questionnaire [14] and EuroQuality of Life 5-Dimension-3 L (EQ-5D-3 L) questionnaire [13]
	Pain relief, as defined by improvement on 100 mm visual analog scale for back and leg pain [15].
	Index level and adjacent disc on magnetic resonance imaging (MRI)
	• by evidence of disc degeneration (Pfirrmann Classification) or osteochondrosis (Modic Changes) [30–32]
	• by numerical measurements in disc high, volumetry, and signal intensity
	• by T2 relaxation
	• by the presence or absence of stenosis.
	Pain medication usage will be assessed by a four-level score (0 = none to 3 = high level of usage).
	Work status and time to return to work
	Neurological status will be evaluated using the Jenny Scale as a neurological test for the lower extremities, including motor and sensory deficits, reflexes, sciatic stretch ability and walking range.
	Functional status:
	• by posture and gait
	• by finger-ground distance
	• by Schober’s sign
	• by precision tenderness/pressure pain

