### Statistical analysis

#### Efficacy variables

The analysis of efficacy variables will focus on estimation of treatment effects and differences between treatment groups. For this purpose, it is assumed that effects of treatment with SC, NDbasic, and NDplus are additive so that treatment effects can be assessed by location shifts (like mean change or median change) between treatment groups. Differences between NDbasic and SC are the total effect of NDbasic, the transplantation/implantation procedure to inject the NDbasic, and the time interval between tissue harvest and transplantation/implantation. Observed differences between NDplus and SC are the total effect of NDplus, the chondrocytes, the transplantation procedure to inject the NDplus, and the time interval between tissue harvest and cell transplantation. Consequently, observed differences between NDplus and NDbasic are assumed the sole effect of chondrocytes. All efficacy data will be presented for patients in the Full Analysis Set (FAS). Primary and secondary efficacy variables and their changes from baseline will be summarized by treatment group. An analysis of variance with factors treatment and the presence or absence of a degenerative adjacent disc (ADD/HD) will be used to evaluate continuous and quasi-continuous, approximately normal data. Confidence intervals will be based on estimated means (least square means) and the corresponding t-statistic. Additional covariates, such as baseline measurements, will be included in the model as appropriate. VAS readings will be summarized by treatment group and visit over the course of the study. MRI parameters and variables to assess functional neurological status will be summarized descriptively. Survival analysis will be used to evaluate time to return to work after surgery. The Kaplan-Meier product-limit estimator will be used to estimate the probability to return to work over time by treatment group for all patients in the FAS. Imputation of missing data has not been planned.

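### The Efficacy variables section assigns MRI measures to descriptive summary, so no between-arm difference with an interval is planned for the disc structure the product is meant to restore

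*Protocol article*

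**What the plan says.** The Efficacy variables section of the protocol article opens with a general aim: "The analysis of efficacy variables will focus on estimation of treatment effects and differences between treatment groups". For the method, an analysis of variance with treatment and adjacent-disc status (ADD/HD) as factors "will be used to evaluate continuous and quasi-continuous, approximately normal data". On intervals it adds: "Confidence intervals will be based on estimated means (least square means) and the corresponding t-statistic". Covariates such as baseline measurements may enter the model as appropriate. For presentation, it says: "Primary and secondary efficacy variables and their changes from baseline will be summarized by treatment group".

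A later sentence of the same section deals with imaging by name: "MRI parameters and variables to assess functional neurological status will be summarized descriptively". No model, contrast or interval is tied to MRI anywhere else in the article.

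Table 1 lists MRI of the index level and the adjacent disc as a secondary outcome. It is assessed "by numerical measurements in disc high, volumetry, and signal intensity", by T2 relaxation, by Pfirrmann and Modic grades, and by presence of stenosis. The Background says that the product "was developed to provide rehydration and maintain the biological integrity of degenerative lumbar discs". The Study design section calls the trial nonconfirmatory and unmasked, takes the self-administered Oswestry Disability Index (ODI) as the primary endpoint, and gives phase II the task of proof of concept and of preparing a confirmatory trial.

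**The concern.** The specific sentence on MRI sits badly with the general rule a few lines above it. Disc height, volumetry, signal intensity and T2 relaxation are numerical secondary outcomes of the kind the analysis-of-variance rule is written for. They are also the only listed outcomes that show disc structure after treatment. Histology concerns the explanted tissue, and the remaining outcomes are patient-reported, functional, neurological, or about medication and work.

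In an unmasked trial with a questionnaire as primary endpoint, it matters whether a difference in reported disability comes with a difference in the disc. Three separate arm summaries leave the reader to form that comparison, without a planned interval and without the adjustment for ADD/HD and baseline that the plan allows for other continuous outcomes. Both proof of concept and the choice of endpoints for a confirmatory trial would draw on an estimated difference and its uncertainty.

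**Working it through.** **1. The text.** Table 1 makes MRI a secondary efficacy outcome, so the general sentences on estimation, model and intervals would cover its numerical measures by default. The MRI sentence then names a different treatment. If the specific sentence overrides the general one, which is the ordinary reading, no contrast with an interval is planned. If it was meant only as an addition, the section does not say so. On either reading it needs a clarifying sentence.

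**2. The plan's own figures.** The article gives no SD, power or precision for any MRI measure. Table 4 (ODI) was reproduced to confirm the arm sizes and the formula.

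- Inputs: n = 60, 36 and 24; SD 12; correlation 0.25 (all from Sample size and power calculation).
- SD of change = 12 × √(2 × (1 − 0.25)) = 14.70.
- Half-width = 1.96 × SD × √(1/n1 + 1/n2).

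| Contrast | Score, SD 12 | Change, SD 14.7 | Power computed (stated) |
|---|---|---|---|
| NDbasic vs SC | 6.20 | 7.59 | 71.9% (71%) |
| NDplus vs SC | 5.68 | 6.96 | 79.5% (79%) |
| NDplus vs NDbasic | 4.96 | 6.07 | 89.1% (89%) |

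All half-widths match Table 4, and power (noncentral t, two-sided 0.05, 10 units) agrees within one point. None of these figures bears on MRI.

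**3. Precision for an MRI measure, in SD units.** Half-width = 1.96 × √(1/n1 + 1/n2):

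- NDplus vs NDbasic: 1.96 × √(1/60 + 1/36) = 0.413
- NDplus vs SC: 1.96 × √(1/60 + 1/24) = 0.473
- NDbasic vs SC: 1.96 × √(1/36 + 1/24) = 0.517

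With a t quantile on 116 residual degrees of freedom (120 patients less 4 parameters) they are 0.418, 0.478 and 0.522.

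**4. What baseline adjustment could add.** By-arm changes from baseline are already planned, so the fair comparison is with change scores. With equal variances at both times and correlation r, the unadjusted half-width is multiplied by √(2(1 − r)) for change scores and by √(1 − r²) with baseline as covariate. For NDplus vs SC:

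| r | Follow-up value alone | Change score | Baseline as covariate |
|---|---|---|---|
| 0.25 (Table 4's value, for ODI) | 0.473 | 0.580 | 0.458 |
| 0.5 (assumed) | 0.473 | 0.473 | 0.410 |
| 0.8 (assumed) | 0.473 | 0.299 | 0.284 |

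The ratio of the last two columns is √((1 + r)/2), that is 0.79, 0.87 and 0.95. The covariate model is never the wider one, but its advantage over change scores shrinks as r rises.

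**5. How many intervals.** Four numerical measures × two discs × three contrasts = 24 per MRI visit.

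**The case against.** The strongest reply is that this is a declared nonconfirmatory trial with the ODI as primary endpoint, reported in a condensed article. Describing secondary imaging outcomes is a legitimate choice in that setting, and detailed models for each measure normally belong in the full protocol or analysis plan. The general sentences do not expressly exclude MRI. The neighbouring sentence on the visual analog scale also speaks only of summaries, and nobody would conclude that pain is outside the model. With 24 intervals per visit and no multiplicity control, restraint has its merits.

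Part of this stands. Model details are not missing merely because the article omits them, and the passage can be read more generously than its plain wording. But nonconfirmatory status argues against formal tests, not against estimates with intervals, and the section itself makes estimation its focus. The MRI sentence also states a choice: it says descriptively, which the pain sentence does not.

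Four stronger inferences are tempting, and the documents do not support them:

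- *The trial will yield no arm difference on MRI.* By-arm summaries of values and changes allow a crude one.
- *The baseline scan goes unused.* Changes from baseline are planned for secondary variables.
- *A later trial could not be sized on MRI.* Arm means, SDs and numbers would serve that purpose.
- *MRI is the trial's only objective outcome.* The article names a core imaging lab but does not say whether its readers are masked, Pfirrmann and Modic grades are judgements, and finger-ground distance and Schober's sign are measured by an examiner.

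**Conclusion.** The point holds in a limited form. As written, the section plans no between-arm difference with an interval for the numerical MRI measures, and this fits poorly with its own stated focus and with the proof-of-concept aim. The change is worth making. It corrects no stated figure and leaves the primary analysis untouched.

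The planned arms would support intervals of roughly 0.4 to 0.5 SD either side of an unadjusted difference. That assumes all 120 patients are analysed with both phases pooled, as in Table 4, with no losses and an approximately normal measure. The gain from baseline adjustment cannot be fixed from the document, because no MRI correlation is given. Sequestrectomy and, in two arms, an injection lie between a pre-operative scan and follow-up, so a high correlation cannot be taken for granted. A reader might also expect a gain from modelling site or scanner. The article gives neither a site variance nor stratification by site, so none is claimed here.

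**What to change.** Replace the MRI part of the sentence with wording to this effect: numerical MRI measures (disc height, volumetry, signal intensity, T2 relaxation), for the index disc and separately for the adjacent disc, are analysed at the scheduled MRI visits with the analysis of variance already specified (treatment, ADD/HD), adding the baseline value of the same measure as covariate. All three pairwise contrasts are reported with 95% intervals and labelled exploratory.

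Add a note that contrasts with SC include the implanted gel itself, so NDplus versus NDbasic is the contrast for the added cells, as the plan already assumes when it attributes that difference to the chondrocytes. Graded MRI items may stay descriptive. Site terms and ordinal models are optional.

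The visit plan figure is not shown, so the MRI time points, and whether every measure was taken at baseline, should be checked against it. The cost is one or two sentences, some extra programming, and more exploratory intervals without multiplicity control. No extra visits or patients are involved if the analysis keeps to scans already scheduled.

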## Methods/design

### Study design

The NOVOCART™ Disc study is a nonconfirmatory, prospective, multicenter, unmasked, randomized study with two phases aimed at gathering preliminary clinical information on NOVOCART™ Disc plus and NOVOCART™ Disc basic used in the treatment of a herniated disc. Phase I aimed to develop a safety profile of the investigational medicinal product NOVOCART™ Disc plus. The objectives of phase II are mainly to provide a basis for a confirmatory clinical trial design and proof of concept. Twelve trial sites are planned to participate in this combined phase-I/II study; three of them have already participated in phase I. In total, 120 patients meeting the inclusion criteria will be randomized, treated according to the randomization, and followed up for 5 years. The primary study endpoint of the phase II is the difference in the Oswestry Disability Index (ODI) between treatment groups 2 years after the intervention. This index has emerged as the most commonly recommended condition-specific outcome measure for spinal disorders. It is a self-administered questionnaire divided into 10 sections designed to assess the limitations of various activities of daily living [11, 12]. The Short Form-36 (SF-36) questionnaire and EuroQuality of Life-5 Dimension (EQ-5D) are applied to assess changes in health status and quality of life [13, 14]. Moreover, changes in leg and back pain are assessed by the Visual Analog Scale (VAS) [15]. Numerical measurements in the disc height, volumetry, and signal intensity of index and adjacent discs and categorical evaluations, such as degeneration scale and the presence or absence of stenosis, are determined by magnetic resonance imaging (MRI). Neurological and functional status and the quantity of current pain medication and time to return to work after surgery are documented. The serology of HIV, hepatitis and *Treponema palladium* are determined preoperatively. Laboratory values (IL-6, Leukotriene, and CRP) as safety vales are being evaluated only in phase I of the study. Adverse events and serious adverse events are documented. Histological investigation of the explanted tissue is performed. Primary and secondary outcome parameters are outlined in more detail in Table 1.

**Table 1 Tab1:** Primary and secondary outcome parameters

Primary outcome parameter	Oswestry Disability Index (ODI), German and Austrian version, at 5 years’ follow-up to measure degenerative lumbar disc-related disability. [11, 12]

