### Sample size and power calculation

The sample size calculation is based on the primary endpoint of the study, which is the group difference in the ODI. A change of 10 units is considered as a clinically meaningful difference. Moreover, a standard deviation of 12 is assumed, based on results of a previous trial (Hägg, Fritzell, Nordwall, 2003). A sample size calculation was performed based on a two-group t-test (nQuery Advisor™ Software, version 7.0). The width of the respective confidence intervals were calculated using a large sample approximation, with 60 patients to be enrolled in the NDplus group, 36 patients in the NDbasic group, and 24 patients in the SC arm (120 patients in total). A detailed power calculation is shown in Table 4.

**Table 4 Tab4:** Power calculation

Treatment group mean / Treatment effect (contrast)	Width of two-sided 95 % confidence interval from point estimate to limit (units in standardized ODI)		Power of pairwise t-test to detect a difference in change from baseline of 10 units in ODI
	ODI sum score (SD = 12 points)	Change in ODI (SD = 14.7 points = 12*sqrt (2(1-r)) when *r* = 0.25	Change in ODI (SD = 14.7 points = 12*sqrt (2(1-r)) when *r* = 0.25
SC (*n* = 24)	4.80	5.88	–
NDbasic (*n* = 36)	3.92	4.80	–
NDplus (*n* = 60)	3.04	3.72	–
NDbasic (*n* = 36) versus SC (*n* = 24)	6.20	7.59	71 %
NDplus (*n* = 60) versus SC (*n* = 24)	5.68	6.96	79 %
NDplus (*n* = 60) versus NDbasic (*n* = 36)	4.96	6.07	89 %

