#### Interim and final analysis

Data collected in the study may be analyzed and reviewed continuously. Early findings may be used to stop the study in case of safety concerns or lack of efficacy or futility with regard to a positive outcome in the NDplus group. To ensure the efficient use of clinical data, interim analyses are being performed (see Table 5).

**Table 5 Tab5:** Interim and final analyses

1st interim analyses	Early evaluation for safety and feasibility, when all 24 patients of phase I are randomized and tissue explants, implant procedures, and 6-week follow-up visits are completed.
2nd interim analyses	Final evaluation for surgical feasibility of the procedures, when all enrolled patients have completed the sequestrectomy and transplantation.
3rd interim analyses	Early evaluation for efficacy with patients who have completed the 12-month follow-up visit.
4th interim analyses	Primary evaluation for efficacy with all patients who have completed the 24-month follow-up visit.
Final analyses	When all patients have completed the scheduled 60-month follow-up visit.

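### The primary ODI comparison is a complete-case estimate at month 24, and Table 4 makes no allowance for patients lost before then

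*Protocol article*

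**What the plan says.** Study design gives the primary phase II endpoint as the "difference in the Oswestry Disability Index (ODI) between treatment groups 2 years after the intervention". (Table 1 puts the primary outcome at 5 years. That conflict is a separate matter; month 24 is used here because Table 5 places the primary efficacy evaluation there.)

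For the analysis, the section Efficacy variables says: "An analysis of variance with factors treatment and the presence or absence of a degenerative adjacent disc (ADD/HD) will be used". Baseline measurements may be added to the model where appropriate. Efficacy is presented for the Full Analysis Set, and "Imputation of missing data has not been planned". In Table 5 the fourth interim analysis is the "Primary evaluation for efficacy with all patients who have completed the 24-month follow-up visit".

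The section Sample size and power calculation computes confidence interval widths "with 60 patients to be enrolled in the NDplus group, 36 patients in the NDbasic group, and 24 patients in the SC arm". Table 4 prints power for the three pairwise comparisons at the same group sizes. The section Randomization gives these as the numbers to be assigned. No allowance for loss is stated.

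**The concern.** An analysis of variance of month-24 ODI without imputation can use only patients whose month-24 ODI was observed. Calling the population the Full Analysis Set does not bring the others back. A patient seen at earlier visits and then lost contributes nothing to the primary contrast, although the earlier scores carry information about where that patient was heading.

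Loss is foreseeable. Randomisation is intraoperative and transplantation follows 90 days later. Table 3 lists exclusions that can arise in between: positive serology after sequestrectomy, and recurrent herniation before transplantation. The second is plausibly related to ODI, and it is tied to a procedure that the surgery-only arm does not have. Up to two years of ordinary attrition follow, in an unmasked trial with a self-administered outcome.

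Two things are at stake. The treatment estimate may be distorted, which matters because the analysis focuses on estimation and phase II is meant to supply the basis for a confirmatory design. And Table 4 gives a reader precision and power for more patients than the analysis may contain.

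**Working it through.** **Inputs.** From Sample size and power calculation and Table 4: difference 10 units; SD 12 for the ODI score; r = 0.25; SD of change 12 × √(2 × (1 − 0.25)) = 14.7; group sizes 60 (NDplus), 36 (NDbasic), 24 (SC). Two-sided α = 0.05 is taken from the two-sided 95% intervals. The loss rate d is an assumption, because the article gives none.

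**Formulas.** SE = SD × √(1/n₁ + 1/n₂). Half-width = 1.96 × SE. Power comes from the noncentral t distribution with n₁ + n₂ − 2 degrees of freedom and noncentrality 10/SE.

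**Step 1: reproduce Table 4.** With SD 14.7 and the full enrolled numbers:

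| Contrast | SE | 10/SE | Half-width (printed) | Power (printed) |
|---|---|---|---|---|
| NDplus–SC, 60/24 | 3.55 | 2.82 | 6.96 (6.96) | 79.5% (79%) |
| NDbasic–SC, 36/24 | 3.87 | 2.58 | 7.59 (7.59) | 71.9% (71%) |
| NDplus–NDbasic, 60/36 | 3.10 | 3.23 | 6.07 (6.07) | 89.1% (89%) |

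The half-widths agree exactly, and the powers agree if the printed values were cut to whole per cent. Table 4's arithmetic is sound. It counts every enrolled patient as evaluable.

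**Step 2: apply an assumed equal loss.** Replace each n by n × (1 − d) and keep SD 14.7. Half-widths grow by 1/√(1 − d).

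| Contrast | Power, d = 10% | d = 15% | d = 20% | Half-width, d = 10% | d = 20% |
|---|---|---|---|---|---|
| NDplus–SC | 75.1% | 72.6% | 69.9% | 7.34 | 7.78 |
| NDbasic–SC | 67.1% | 64.6% | 61.8% | 8.00 | 8.49 |
| NDplus–NDbasic | 85.7% | 83.6% | 81.3% | 6.40 | 6.79 |

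**Step 3: the same loss with baseline adjustment.** At the article's own r = 0.25 the residual SD is 12 × √(1 − 0.25²) = 11.6. Degrees of freedom are kept at n₁ + n₂ − 2, a slight simplification.

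| Contrast | d = 20% | d = 30% | Printed |
|---|---|---|---|
| NDplus–SC | 88.1% | 83.4% | 79% |
| NDbasic–SC | 81.6% | 76.0% | 71% |
| NDplus–NDbasic | 95.0% | 92.0% | 89% |

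**Step 4: scale of a possible bias.** This is an illustration only; both inputs are assumed. If SC loses x percentage points more patients than NDplus, and those patients' unobserved ODI would be 15 units worse than that of patients who stay, the contrast shifts by about x/100 × 15. That is 0.75 units at x = 5, 1.5 at x = 10 and 3.0 at x = 20. In this scenario the observed SC mean looks too good, so the shift works against NDplus. If NDplus loses more such patients, the sign reverses.

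**The case against.** **The Table 5 row may only be a trigger for the data cut.** Other rows of that table are worded as triggers, and the article names the Full Analysis Set for efficacy. This is a fair reading, and the article does not itself call the analysis a single-visit one. It changes little: an analysis of variance of the month-24 score without imputation still uses only observed month-24 scores.

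**The power is still there.** A reader might infer that the printed power cannot be reached once any month-24 ODI is missing. The article does not support that. It holds only for the unadjusted change-score t-test behind Table 4. With the baseline covariate that the article allows, power exceeds the printed figures even at 30% loss (step 3). Using the ODI score with SD 12, it is about 86, 79 and 94% at 20% loss, in the order of the tables above. What stands is narrower: no loss allowance is stated, and Table 4 does not rest on an adjusted model, which is itself left optional.

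**The bias is speculative.** A reader might also infer that the estimate is biased whenever loss depends on earlier ODI, or that it favours the product. Neither follows. If baseline ODI is in the model, dependence on baseline alone need not bias the contrast. Dependence on later ODI distorts it mainly when it differs by arm. The article has no loss data, and the natural illustration runs against NDplus. The risk remains; its size and sign are unknown.

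**The trial is nonconfirmatory, and other documents may say more.** True, and this lowers the weight of the power point, since no target power is stated. An analysis plan might define the analysis set or add sensitivity analyses. But the absence of imputation is stated in the article, and estimation is the declared aim.

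**Conclusion.** The point holds in two parts.

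First, the primary ODI contrast is a complete-case estimate. It can be biased if loss depends on post-treatment ODI and differs between arms. The design makes that possible, but the article gives nothing from which to size it or fix its direction.

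Second, Table 4's intervals and powers hold only with no loss at all. On its own basis, an assumed 10 to 20% loss costs roughly 3 to 10 percentage points of power, depending on the contrast, and widens the intervals by about 5 to 12%. This is a fault in what the table represents, not evidence that the trial is underpowered: a baseline-adjusted analysis at r = 0.25 would give about 88, 82 and 95% at 20% loss.

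The power results assume equal proportional loss in all arms, two-sided 5% tests and the article's SD and correlation. For a nonconfirmatory trial this should be corrected, but it does not undermine the design.

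**What to change.** 1. Analyse ODI with a baseline-adjusted mixed model for repeated measures on all randomised patients, using every scheduled post-baseline ODI, with the ADD/HD factor kept and the treatment contrast read at month 24.
2. Reword the fourth row of Table 5 so that the primary evaluation covers all randomised patients and is run once the last of them has reached month 24.
3. Restate Table 4 on expected evaluable numbers, with the assumed loss rate given, and for the model actually used. Depending on that choice, the figures may fall below or rise above the printed ones.

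The cost is a little more analysis work and reliance on a missing-at-random assumption, which is weaker than what the complete-case analysis needs but still untestable. A patient with no post-baseline ODI adds nothing to such a model beyond being counted, so the number of these should be reported by arm. No new patients or data are required.
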